### Crossbow needle group

Before treatment, a prescription of herbs containing Sheng Cao Wu (*Radix Aconiti Kusnezoffii*) (20 g), Tou Gu Xiang (*Gaultheria yunnanensis*) (50 g), Hei Gu Teng (*Periploca forrestii*) (30 g), and Ba Jiao Feng (*Alangium chinense*) (15 g) will be ground into a powder, put into a glass container, and soaked in 1000 mL of 50%-proof white liquor for seven days. The obtained clear brown liquid is effective in dispelling wind and eliminating dampness, dispersing numbness and relieving pain, dredging collaterals, and promoting blood circulation [15–18]. Patients in this group will receive crossbow needle therapy. The treatment will use 0.22 × 1.0-mm skin needles (Cloud & Dragon Medical Device Co., Ltd., Wujiang, Zhejiang, China). A practitioner will soak the skin needles in the brown herbal liquid for 10 min before treatment. Patients will be asked to take a supine or sitting position. The soaked skin needles will be applied on the square knee area formed by Xuehai (SP10), Liangqiu (ST34), Yanglingquan (GB34), and Yinlingquan (SP9), with the patella as the center, moving in different directions (Fig. 3). One completion of rolling the skin needle in all directions as displayed in Fig. 3 is seen as one set of application. Skin needles will be dipped into 5 mL of herbal liquid every five sets of application until the liquid is used up. The intensity of application varies from person to person, depending on the tolerance of the patients.

**Fig. 3 Fig3:**
[figure not shown]
Crossbow needle treatment. The *red arrows* indicate the rolling directions of the skin needle. In the container beside the leg is the herbal liquid

### Acupuncture group

The acupuncture group will be treated with 0.30 × 40 mm and 0.30 × 50 mm disposable sterilized filiform needles (Suzhou Medical Appliance Co., Ltd., Suzhou, Jiangsu, China) applied to Dubi (ST35), Neixiyan (EX-LE4), Xuehai (SP10), Liangqiu (ST34), Yanglingquan (GB34), and Ashi points. The selection of the points is based on the basic theory of acupuncture therapy [22] to treat KOA. Practitioners will perform the treatment according to the national standard of acupuncture manipulation [23–25]. Needles will be inserted and manually manipulated until *de qi* is achieved.

### Combined use of drugs

During the whole period of observation, it is suggested that the patients do not use drugs or other methods for the treatment of KOA in addition to the experimental scheme. During the treatment period, if the patients take medication by themselves or use other methods of treatment due to aggravated symptoms and unbearable knee pain, they will be withdrawn from the trial. The clinicians will make the appropriate treatments according to the specific conditions of the patient until the symptoms are improved.

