**Methods/design:**

The trial is a randomized, multicenter, parallel, non-inferiority study. Three hundred and six patients will be randomly assigned to a crossbow needle group (*n* = 153) and an acupuncture group (*n* = 153). Patients in each group will receive treatment every other day, three times a week, 20 times in total. Follow-up will be conducted 15 days and 30 days after treatment. The primary outcome will be the Western Ontario and McMaster Osteoarthritis Index (WOMAC) score at baseline, the end of treatment, first follow-up, and second follow-up. The secondary outcomes will include Lysholm knee score, Japanese Orthopedic Association (JOA) knee score, visual analogue scale (VAS), and the MOS 36-item short-form health survey (SF-36).

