### Sample size

The trial is designed to determine the efficacy of crossbow needle therapy on KOA and prove that its clinical efficacy is not inferior to normal acupuncture therapy; therefore, we chose a non-inferiority trial design [21]. Sample size calculation is based on the formula $$ n=2{\left[\frac{\left(\mu \alpha +\mu \beta \right)s}{\delta}\right]}^2 $$, in which μα and μβ are constants and *s* is the combined standard deviation. We set *α* at 0.05 (one-sided), *β* at 0.10, *δ* at 1.5, and *s* at 4.0 (*δ* and *s* based on expert consensus to determine the formula parameters, but not clear as currently), with *μα = μ*_0.05_ = 1.645 and *μβ = μ*_0.10_ = 1.282. After calculation, the sample size of each group should be around 122. Assuming a 20% dropout rate, each group needs at least 153 patients; 306 patients will be recruited in the trial.

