### Interventions

Patients in both groups will receive two sessions (ten times a session) of treatment. The treatment will be performed every other day, three times per week, 20 times in total. The first follow-up will be conducted 15 days after the last treatment, followed by a second follow-up 15 days later. All practitioners involved in the trial are trained and registered professionals. A training program to standardize all manipulations and filling of a case report form (CRF) will be provided before the trial. Investigators will inform all patients about the possible inconveniences from the trial.

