### Adherence

Before the start of the trial, the investigators will fully inform the patients of the benefits and the possible inconvenience of the study. The patients will sign the informed consent form and volunteer to participate in the study. Anteroposterior and lateral X-ray of the knee, laboratory examination, and two courses of treatment will be free of charge in order to improve the adherence of the patients. The baseline data of each patient (name, gender, age, address, telephone or contacts of immediate family members) will be recorded in detail, hereby to facilitate the supervision of patients’ adherence. The cases of drop-out, withdrawal, and discontinuation will be recorded and followed up by telephone or even followed up at patients’ homes if necessary.

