### Statistical analysis

Data analysis will be conducted in accordance with the intention-to-treat principle. Missing data will be handled using linear mixed effects models. Statisticians and chief investigators will work out an analysis plan and related forms before database lock. The analysis will include case distribution, comparison of basic values, compliance, effectiveness, factors that influence efficacy, and safety. Statistical analysis will be conducted using SAS 9.2 (SAS Institute Inc., Cary, NC, USA). The Wilcoxon rank sum test, *t* test, or variance analysis will be performed for inter-group or intra-group comparison according to data distribution. The Wilcoxon rank sum test will be used to compare ranked data. The chi-square test will be applied to compare enumeration data. All tests will be one-sided. A *p* value < 0.05 will be considered statistically significant.

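### Patients who turn to other treatment for unbearable pain leave the trial before any scheduled post-baseline WOMAC, which can bias toward non-inferiority if crossbow needle therapy is worse

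*Protocol article*

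**What the plan says.** The Combined use of drugs section advises against other treatment for the knee throughout observation. For patients who nevertheless use it during the treatment period, the consequence is fixed: "due to aggravated symptoms and unbearable knee pain, they will be withdrawn from the trial". It adds: "The clinicians will make the appropriate treatments according to the specific conditions of the patient until the symptoms are improved".

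The other relevant provisions are:

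- Interventions: "The treatment will be performed every other day, three times per week, 20 times in total".
- Abstract, Methods/design: the primary outcome is the WOMAC "score at baseline, the end of treatment, first follow-up, and second follow-up".
- Adherence: "The cases of drop-out, withdrawal, and discontinuation will be recorded and followed up by telephone", with home visits if needed. No outcome measure is named for this contact.
- Sample size: "Assuming a 20% dropout rate, each group needs at least 153 patients; 306 patients will be recruited in the trial".
- Statistical analysis: "Data analysis will be conducted in accordance with the intention-to-treat principle", and "Missing data will be handled using linear mixed effects models".

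**The concern.** The rule acts only during treatment, and on the schedule shown no primary outcome is measured in that window. A patient removed under it contributes a baseline WOMAC and nothing afterwards. A linear mixed model then in effect treats that patient like others in the same arm with a similar baseline who stayed in. That is reasonable if leaving is unrelated to the later score once baseline is known. Here the stated trigger is worsening after baseline, which no recorded WOMAC captures.

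The direction matters because this is a non-inferiority trial. If crossbow is worse, one rule applied to both arms removes more of the crossbow patients who did badly. The remaining arms look more alike, and a small difference is what supports the claim. The 20% dropout allowance protects power; it does nothing against this bias. A later analysis plan can change how the data are modelled, but it cannot supply scores that were never collected.

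**Working it through.** **Plan's own figure.** With one-sided alpha 0.05, beta 0.10, margin 1.5 and SD 4.0: n = 2 × [(1.645 + 1.282) × 4.0 / 1.5]² = 121.8, so 122 per arm; 122 / 0.80 = 152.5, so 153. Both stated figures reproduce.

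**Timing.** 20 sessions / 3 per week = 6.7 weeks, with the first post-baseline WOMAC at the end.

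**Model.** The protocol gives no rescue or withdrawal rates, so the following is an illustration.

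- From the protocol: 153 per arm, SD 4.0, margin 1.5, higher WOMAC is worse. The margin and SD are taken to be in WOMAC points; the Sample size section does not name the scale.
- Assumed: crossbow is truly worse by exactly 1.5. On-treatment state Z and final score Y both have mean 0 (acupuncture) and 1.5 (crossbow), with correlation r.
- Assumed: a rescue threshold that 10% of acupuncture patients exceed, c = 1.2816 × 4 = 5.13. In the crossbow arm the standardised threshold is (5.13 − 1.5) / 4 = 0.907, exceeded by 18.2%.
- Assumed: a share q of those above the threshold use other treatment and are withdrawn. At q = 50% this is 5.0% versus 9.1%.

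**Closed form without baseline adjustment, r = 0.7, q = 50%.** The mean of those remaining is μ − q·r·SD·φ(a) / (1 − qP), where a is the standardised threshold, φ the normal density and P the proportion above it.

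- Acupuncture: 0 − 0.5 × 0.7 × 4 × 0.1755 / 0.950 = −0.259.
- Crossbow: 1.5 − 0.5 × 0.7 × 4 × 0.2645 / 0.909 = 1.093.
- Observed difference: 1.093 + 0.259 = 1.35 instead of 1.50; SE 0.458.
- False non-inferiority: Φ((1.5 − 1.351) / 0.458 − 1.645) = Φ(−1.32) = 9.3%, against 5% with no withdrawal.

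**With baseline adjustment.** This is closer to the planned mixed model when withdrawn patients have only a baseline. Baseline is assumed to correlate 0.5 with Z and Y; 40,000 simulated trials per cell. False non-inferiority:

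| r | q = 25% | q = 50% | q = 75% | q = 100% |
|---|---|---|---|---|
| 0.5 | 5.7% | 6.7% | 7.8% | 9.7% |
| 0.7 | 6.3% | 8.5% | 10.9% | 15.2% |
| 0.85 | 6.8% | 9.4% | 14.3% | 21.9% |

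With no withdrawal the same code gives 5.0 to 5.3%. Repeat runs agreed within simulation error.

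**Sensitivity to the assumptions.**

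- r = 0: no inflation. Arms truly equal: bias in the difference −0.004, that is, none.
- Only half the deficit present when rescue occurs: 5.5% (q = 50%) and 7.1% (q = 100%) at r = 0.5; 6.6% and 8.9% at r = 0.7.
- Rarer withdrawal, 1% versus 2.5%: 5.9% (r = 0.5) to 7.1% (r = 0.7).
- Every patient above the threshold withdrawn, in a separate simulation with a weaker link between baseline and on-treatment state, r = 0.5 to 0.8: 8 to 11% at 3% versus 7% withdrawn, 10 to 15% at 5% versus 10%, and 12 to 21% at 10% versus 18%.
- Reverse case, 18.2% of acupuncture and 10% of crossbow patients above the threshold, no true difference, r = 0.7, unadjusted: power falls from 94.9% to 90.4% (q = 50%) or 81.3% (q = 100%).

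**Would collecting later scores be enough?** Unadjusted, r = 0.7, q = 50%: using only post-rescue scores gives 15.1% if rescue brings patients to the acupuncture mean, 11.0% at 2 points above it and 7.7% at 4 points above, against 9.3% under the present rule. So post-rescue scores alone can also favour non-inferiority. Using the score taken at report, before rescue, gives 3.9% (q = 50%) and 2.9% (q = 100%) with baseline adjustment.

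**The case against.** The best case for the plan has four parts.

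- *A WOMAC may be taken after all.* The schedule used here is the one in the abstract, the SPIRIT figure (Fig. 2) is not shown, investigator A collects data at each visit, and withdrawn cases are contacted. An early-termination WOMAC in Fig. 2 would reduce the problem. This stands as a caveat. Still, nothing shown commits to a WOMAC after withdrawal, and one taken only after the clinician has treated the patient would reflect rescue.
- *Sensitivity analyses belong in the analysis plan, which is deferred to before database lock.* This stands for the choice of analysis. It does not answer the withdrawal rule, which the protocol itself fixes and which decides whether data exist to analyse.
- *The size is assumed.* This stands. The inflation is small if withdrawals are rare or the deficit appears late. A reader might seize on a worst case: with correlation 1, every patient above the threshold withdrawn and no baseline adjustment, the model gives 36%. The documents support none of those extremes.
- *The direction is not fixed.* This also stands. A reader might infer that the rule necessarily favours crossbow. It does so only if crossbow is worse and on-treatment worsening predicts the final score.

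A reader might also infer that these patients are dropped from the randomised comparison. The text does not say so: the analysis follows intention to treat, and nobody leaves the assigned arm. What is lost is their outcome.

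**Conclusion.** The point holds as a conditional risk of bias created by a stated rule. Patients are removed because they worsened, before any post-baseline WOMAC on the visible schedule, and the intention-to-treat mixed model must then lean on a doubtful missing-at-random assumption. With a true difference at the margin, about 5% versus 9% withdrawn and correlation 0.5 to 0.85, false non-inferiority is about 7 to 10% against a nominal 5%. That range rests on assumed rates and correlations and shows what could happen; it is not an estimate for this trial. It should be fixed, with medium confidence, because Fig. 2 is not visible and no withdrawal rates are given.

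**What to change.** In Combined use of drugs, replace withdrawal from the trial with discontinuation of study treatment. Then:

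- Have investigator A take WOMAC when other treatment is reported, before clinician rescue where possible, and again at end of treatment and both follow-ups, using the contact already provided under Adherence.
- Record the date and type of other treatment, and keep these patients in the intention-to-treat analysis.
- Add a supportive sensitivity analysis that scores rescued patients at the WOMAC taken at report, with baseline used only where no such value exists. In the illustration (r = 0.7) its error stays below 5%, and power at no true difference goes from about 98% to no lower than 97.4%. The value at report may already reflect self-medication, which is one reason to keep this analysis supportive.

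Do not make the worse of the report and baseline scores decisive. Its power cost grows with improvement from baseline: about 94 to 96% power remains if patients improve by 6 points and 80 to 90% at 12 points. It also over-corrects, with error at 12 points of 1.1% (q = 50%) and 0.4% (q = 100%).

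The cost is a short amendment, a few extra WOMACs by existing staff and one extra analysis; the sample size is unchanged. The trial was already recruiting, with its end expected in May 2018, so the change helps only patients still in the trial when it takes effect. Outcomes of those already withdrawn cannot be recovered.

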### Outcome measures

#### Primary outcome measures

We will use the Western Ontario and McMaster Universities Osteoarthritis Index (WOMAC) as the primary outcome measure [26]. The WOMAC is a questionnaire composed of 24 questions to assess physical functional disability. It was developed for patients with osteoarthritis of the hip or knee and measure three subscales: pain; stiffness; and physical function. Higher scores indicate more severe symptoms or physical disability. The Nimodipine method will be applied to calculate the efficacy.

#### Secondary outcome measures

The Lysholm knee score will be used to assess knee function of the patients. The score is rated 0–100, with 25 points attributed to pain, 15 to locking, 10 to swelling, 25 to instability, 10 to stair climbing, and 5 each to squatting, limp, and support.

The Japanese Orthopedic Association (JOA) score is a frequently used scale. It comprises ratings of pain (40 points), range of motion (20 points), gait (20 points), and activities of daily living (20 points). The JOA score will be used to assess the therapeutic effect, with a higher score indicating better effect.

The visual analogue scale (VAS) will be applied to evaluate the pain intensity of the patients. It is a standard tool in pain studies to measure pain intensity. The score is in the range of 0–100 (0 indicating no pain and 100 indicating the worst pain imaginable).

The MOS 36-item short-form health survey (SF-36) will be used to assess the patients’ living standard before and after treatment. The health survey consists of eight dimensions: physical function; role limitations due to physical problems; bodily pain; general health; vitality; social function; role limitations due to mental problems; and mental health. Higher scores represent better quality of life.

### Adherence

Before the start of the trial, the investigators will fully inform the patients of the benefits and the possible inconvenience of the study. The patients will sign the informed consent form and volunteer to participate in the study. Anteroposterior and lateral X-ray of the knee, laboratory examination, and two courses of treatment will be free of charge in order to improve the adherence of the patients. The baseline data of each patient (name, gender, age, address, telephone or contacts of immediate family members) will be recorded in detail, hereby to facilitate the supervision of patients’ adherence. The cases of drop-out, withdrawal, and discontinuation will be recorded and followed up by telephone or even followed up at patients’ homes if necessary.

### Data monitoring and management

Our study group will set up a special data monitoring committee for data management and quality control, which consists of hospitals, company, and institute.

#### Quality control system

All three-level quality monitoring system was established. Clinical research associates (CRAs) were assigned for data monitoring. Level 1 monitoring requires the CRAs in the three hospitals (No. 1 Affiliated Hospital of Guiyang University of Chinese Medicine, No. 2 Affiliated Hospital of Guiyang University of Chinese Medicine, and Chinese Medicine Hospital of Qiandongnan Miao and Dong Autonomous Prefecture) to monitor the quality of the CRFs once a week, fill out the monitoring report, and report to the principal investigator (PI) in time. Level 2 monitoring requires the CRA from CLINDA Soft Co., Ltd. to conduct quality monitoring once every six months, fill out the monitoring report, and report to the project leader of CLINDA in time. Level 3 monitoring requires the person in charge or the technical backbone at the Institute of Basic Research in Clinical Medicine, China Academy of Chinese Medical Sciences to monitor once or twice annually.

#### Data management platform

The data management platform was set up by CLINDA Soft Co., Ltd. It includes the IWR and EDC systems. It includes nine modules, including data entry and statistics. All data will be entered using a double-entry procedure performed by two different individuals.

### Statistical analysis

Data analysis will be conducted in accordance with the intention-to-treat principle. Missing data will be handled using linear mixed effects models. Statisticians and chief investigators will work out an analysis plan and related forms before database lock. The analysis will include case distribution, comparison of basic values, compliance, effectiveness, factors that influence efficacy, and safety. Statistical analysis will be conducted using SAS 9.2 (SAS Institute Inc., Cary, NC, USA). The Wilcoxon rank sum test, *t* test, or variance analysis will be performed for inter-group or intra-group comparison according to data distribution. The Wilcoxon rank sum test will be used to compare ranked data. The chi-square test will be applied to compare enumeration data. All tests will be one-sided. A *p* value < 0.05 will be considered statistically significant.

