### Randomization and blinding

There are two investigators at each center (referred to as A and B). Investigator A is responsible for entering baseline data of patients and perform randomization, but he will not know the grouping details and will not participate in the treatment. Investigator B is responsible for performing treatment according to the grouping. At each visit, A is responsible for collecting data and entering the data in the electronic data capture (EDC) system. The therapist and the data collector are separate. Statisticians are responsible for data processing and are not aware of the grouping until the end of the trial. Central randomization will be conducted by CLINDA Soft Co., Ltd. (Tianjin, China). A random sequence will be generated with SAS 9.2 (SAS Institute, Inc., Cary, NC, USA) by an independent statistician who is not involved in the study; the sequence will be stored in a central randomization system (interactive web response [IWR] system). Patients will be stratified based on the three different centers and randomly assigned to the crossbow needle group and the acupuncture group in a 1:1 ratio. The crossbow needle group will receive crossbow needle therapy. Regular acupuncture therapy will be performed on the acupuncture group.

In this trial, patients will not be blinded due to the uniqueness of the two therapies. Investigators and statisticians will be blinded. Treatment, data collection, and data analysis will be conducted by trained practitioners, data collectors, and statisticians, respectively, all blinded to one another in order to ensure the reliability of the results.

The conditions for unblinding are: (1) infection or other adverse events (AE)—and these patients will be withdrawn from the trial; or (2) the end of the trial and data analysis.

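### The between-arm tests named for WOMAC make no use of the baseline WOMAC score as a covariate, so the non-inferiority comparison is less precise than the collected data allow.

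*Protocol article*

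**What the plan says.** - **Data collected.** The abstract gives the primary outcome as the "Western Ontario and McMaster Osteoarthritis Index (WOMAC) score at baseline, the end of treatment, first follow-up, and second follow-up". Under Randomization and blinding, "Investigator A is responsible for entering baseline data of patients and perform randomization", so a pre-treatment value should exist for each patient.
- **Tests named.** The Statistical analysis section says: "The Wilcoxon rank sum test, *t* test, or variance analysis will be performed for inter-group or intra-group comparison according to data distribution". No covariate accompanies any of these.
- **Mixed model.** The same section says: "Missing data will be handled using linear mixed effects models". That is its only stated role, and its terms are not given.
- **Derived measure.** Under Primary outcome measures: "The Nimodipine method will be applied to calculate the efficacy". No formula follows.
- **Sample size.** The design is non-inferiority. The calculation uses the standard formula for two unadjusted means, with the inputs "We set *α* at 0.05 (one-sided), *β* at 0.10, *δ* at 1.5, and *s* at 4.0". It has no term for correlation with baseline.

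**The concern.** A patient's WOMAC after treatment can be expected to correlate with the same patient's WOMAC before treatment. A rank sum test, a t test or a plain analysis of variance on follow-up scores leaves that predictable variation in the error term. It also lets a chance difference between arms at baseline shift the estimate, by that difference multiplied by the slope of follow-up on baseline.

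This matters in a non-inferiority trial because the conclusion depends on how far the one-sided confidence limit lies from the estimate, relative to a fixed margin. A wider interval raises the chance of missing non-inferiority that is really there. An uncorrected imbalance can move the estimate towards or away from the margin.

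Analysing change from baseline is not an equivalent remedy. It forces the slope to be 1 instead of estimating it, and so over-corrects when the true slope is smaller. The secondary scales lose precision in the same way wherever their baseline value is collected. The point concerns the baseline value of the outcome only, not adjustment for centre.

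**Working it through.** **Inputs from the Sample size section.** Margin δ = 1.5, SD s = 4.0, one-sided α = 0.05 (z = 1.645), β = 0.10 (z = 1.282), 20% dropout, 1:1 allocation. The true difference is taken as 0, as the formula implies.

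**Assumed, not in the article.** The correlation ρ between baseline and follow-up WOMAC, taken from 0.3 to 0.7; equal SDs at the two times; and δ and s both in WOMAC points. The article does not say whether s is the SD of the follow-up score or of the change, so both readings are worked.

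**1. The plan's own figure.** n = 2[(1.645 + 1.282) × 4.0 / 1.5]² = 121.85, so 122 per arm. 122 / 0.8 = 152.5, so 153 per arm and 306 in total. The stated figures reproduce.

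**2. Unadjusted comparison at 122 per arm.** SE = 4.0 × √(2/122) = 0.512. Distance from estimate to one-sided 95% limit = 1.645 × 0.512 = 0.84. Power = Φ(1.5/0.512 − 1.645) = 90.0%.

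**3. Baseline-adjusted comparison at 122 per arm.** The residual SD is
- reading A (s is the SD of the follow-up score): s√(1 − ρ²);
- reading B (s is the SD of change): s√((1 + ρ)/2).

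| ρ (assumed) | Reading | Residual SD | Distance to limit | Power | n per arm for 90% |
|---|---|---|---|---|---|
| unadjusted | A or B | 4.00 | 0.84 | 90.0% | 122 |
| 0.3 | A | 3.82 | 0.80 | 92.3% | 111 |
| 0.5 | A | 3.46 | 0.73 | 95.9% | 92 |
| 0.7 | A | 2.86 | 0.60 | 99.3% | 63 |
| 0.3 | B | 3.22 | 0.68 | 97.7% | 80 |
| 0.5 | B | 3.46 | 0.73 | 95.9% | 92 |
| 0.7 | B | 3.69 | 0.78 | 93.7% | 104 |

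For example, at ρ = 0.5 under reading A: SE = 0.512 × √0.75 = 0.444, and power = Φ(1.5/0.444 − 1.645) = 95.9%, a gain of 5.8 points. Under reading A the gain is 3.9 points at ρ = 0.4 and passes 5 points at about ρ = 0.46.

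**4. No dropout.** With 153 evaluable per arm and ρ = 0.5, power goes from 94.9% to 98.4%, a gain of 3.5 points.

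**5. Does a change score recover the loss?** If s is the follow-up SD, the change score has variance 2(1 − ρ)s². At ρ = 0.5 this equals s², so power stays at 90.0%. At ρ = 0.3 the variance is 1.4s² and power falls to 79.7%. At ρ = 0.7 it is 0.6s² and power is 98.4%, still below the 99.3% from adjustment.

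**6. Does percentage change recover it?** If the Nimodipine method means relative change from baseline (an assumption), baseline enters as a divisor. In an illustrative simulation (baseline mean 40, SD 12 or 8, follow-up mean 25, ρ from 0.3 to 0.7, all assumed), percentage change had 0.68 to 0.93 of the efficiency of ANCOVA.

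**7. A larger SD.** The Sample size section concedes that δ and s rest on expert opinion and are not well established. If s were 5.0 (for illustration), power at 122 per arm would be Φ(1.5/0.640 − 1.645) ≈ 76% unadjusted. At ρ = 0.5 under reading A, the adjusted figure is Φ(1.5/0.554 − 1.645) ≈ 86%.

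**The case against.** The strongest reply has three parts.

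*It is a matter for the SAP.* The article is condensed and says an analysis plan will be written before database lock. Model terms usually belong there, and nothing in the text forbids a baseline term. Analysis of variance and the mixed model can both carry one, and the article separately plans to examine what influences efficacy. It is true that the door is open. But the article does more than stay silent: it names the tests for comparing groups, two of the three cannot take a covariate, and nothing ties the mixed model or the search for influential factors to baseline WOMAC in the non-inferiority comparison. The criticism is of a choice that was stated.

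*Baseline may already be used through the Nimodipine method.* A test on a change or percentage measure does use baseline, and the follow-up-score calculation would then not describe the loss exactly. This stands as a limit on the size. Steps 5 and 6 show that such measures do not in general match covariate adjustment.

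*Nothing planned is lost.* In a 1:1 randomised trial the unadjusted comparison is unbiased and keeps its type I error rate. The sample size was computed for it, and it delivers 90%. The gain also depends on a correlation that the article does not give: it is 2.3 points at ρ = 0.3 under reading A, and smaller at ρ = 0.5 if more than 122 per arm are evaluable. All of this is correct. It makes the point one of efficiency, not validity, but does not answer why precision available from data already collected should be given up.

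**Conclusion.** The concern holds. The article collects baseline WOMAC and names between-arm tests that do not adjust for it. The direction is secure: adjustment helps for any non-zero correlation if follow-up scores would otherwise be compared, and for any correlation below 1 if change scores would be.

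The size is not fixed by the article. With 122 evaluable per arm and assumed correlations of 0.3 to 0.7, power rises from 90.0% to between 92.3% and 99.3%. The unadjusted limit then lies about 5% to 40% further from the estimate than the adjusted one (0.84 against 0.80 to 0.60) if 4.0 is the SD of the follow-up score. If 4.0 is the SD of change, power rises to between 93.7% and 97.7%. These figures assume equal SDs at baseline and follow-up, a true difference of zero, and a margin and SD in WOMAC points. This is an avoidable loss of efficiency. It is not a bias, and the sample size calculation is not in error.

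**What to change.** In the Statistical analysis section, or in the analysis plan due before database lock, name a baseline-adjusted model as the primary between-arm analysis of WOMAC. Either of these serves:

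- ANCOVA of the post-baseline WOMAC score with treatment and baseline WOMAC as terms; or
- the linear mixed model already named, over the post-baseline visits, with treatment, visit, their interaction, and baseline WOMAC allowed to act differently by visit.

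State that the one-sided 95% limit of the adjusted treatment difference, in WOMAC points, is compared with the 1.5-point margin. Use the same form for each secondary scale, with that scale's own baseline value. Keep the rank sum test, t test and unadjusted analysis of variance as supportive only. Fix the wording before treatment allocation is disclosed to the statisticians.

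The cost is one sentence. Baseline WOMAC is already collected, the target of 306 can stand, and one degree of freedom per covariate is negligible at this sample size.
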